## Methods

This is a study of DBS targeting the NAcc in up to six patients with SE-AN, using pre- and post-operative repeated measures. To date, five patients have been enrolled in the study.

The study period is 15 months—see Figure 1 for details of study interventions. There will be pre-operative assessments in month 1, the DBS operation in month 2, followed by the DBS switch-on at the end of month 3. DBS dose will be optimised during months 3–6. During month 10 of the study (6 months after switch-on), there will be two double-blinded 2-week periods of DBS on/off as described by Denys et al. (53). At 15 months (12 months after switch-on), there will be final follow-up tests. This study is a quantitative and qualitative investigation of eating disorder and co-morbid pathology, using MEG to image neural processes, and computerised tasks to assess habit formation. There is also a parallel quantitative and qualitative sub-study of ethical issues involved.

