#### Phase IV: Post-operative Follow-up Phase

##### Post-operative Assessments, Aiming to Track the Neural and Symptomatic Change As a Result of DBS, Will Involve

*Weekly* Self-report-rating scales of eating disorder psychopathology, anxiety and depression involving the True Colours text-messaging system started in phase I: http://oxtext.psych.ox.ac.uk/true-colours (5 min) (see Phase II: True Colours) (see Figure 1 for more details). Weekly side effects questionnaires, the SAFTEE-SI (81) and DBS side effects questionnaire (82).

Monthly

Interview with [name] and [name]. Repeat of baseline measures collected pre-operatively [see Phase II: Assessment with Research Team (Repeated at All Subsequent Monthly Follow-ups)].Joint neurosurgery–psychiatry reviews with [name] and [name], senior nurse practitioner and [name]. During this review, neurosurgical parameters (such as the degree of stimulation) and psychiatric parameters (such as experience of eating disorder and co-morbid psychiatric symptoms) will be jointly assessed. Any necessary adjustments to stimulator intensity will then be programmed.

Post-operative Neuroimaging

Resting state and food “wanting” task under MEG (13), at OHBA, at month 3 (pre-DBS switch-on), two scans in month 10 in DBS on and off conditions and at the end of study in month 15. Post-operative MRI is not possible with the stimulator implanted for safety reasons.Following each MEG scan, participants will carry out the LOFPQ food reward task. Tasks from the CANTAB (80) and a task measuring habit formation (50) will be carried out twice during the DBS on-off phase and at the end of the study (see Figure 1).

Post-operative neuropsychological assessment at 15 months (12 months after DBS switch-on) will be a repeat of those tests detailed in Section “Phase II: Neuropsychological Assessment.”

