### Data Analysis

Number of participants: this is an exploratory study of up to six patients, and therefore a precise power calculation is not possible. External review of the protocol for an initial single patient pilot (by the international expert in the neuroscience of AN, [name], University of San Diego) suggested the scientific importance of extending the study to include more patients.

Treatment effects will be established using within-subject analyses comparing baseline characteristics with patient assessment at each monthly follow-up session and by comparing change in symptoms during periods when the stimulator is “on” and periods when the stimulator is “off.” We plan to use multiple regression, analysis of variance and *t*-tests using SPSS software to analyse the data. Results can be compared to our published findings from a linked multimodal neuroimaging case–control study of reward processing in current AN, recovered AN and controls (12, 13, 36).

In addition, MEG data will be analysed using in-house software and open software packages. Preprocessing of data will rely on propriety software supplied by the scanner manufacturer. We will employ both signal and source space methods, building on our previous approach to analysing and interpreting neural data obtained in patients with AN. Non-parametric statistics and general linear modelling will be used to establish significance.

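### The comparison of baseline with each monthly follow-up starts before surgery, so it measures implantation, peri-operative care and time together with stimulation; the scheduled pre-switch-on data should be named as a second reference.

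*Protocol article*

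**What the plan says.** The Data Analysis section of the protocol article states: "Treatment effects will be established using within-subject analyses". It names two routes to a treatment effect. The first is "comparing baseline characteristics with patient assessment at each monthly follow-up session". The second works "by comparing change in symptoms during periods when the stimulator is" on and periods when it is off. Neither is given priority. The MEG analysis is described in a separate paragraph that names no reference scan.

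The timing is in the Methods section: "There will be pre-operative assessments in month 1", then "the DBS operation in month 2, followed by the DBS switch-on at the end of month 3". During month 10 "there will be two double-blinded 2-week periods of DBS on/off". Final tests are at month 15.

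Three sets of measurements bear on the interval between surgery and switch-on:

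- **MEG and the food reward task.** Under Phase IV, the first post-operative MEG scan is placed "at month 3 (pre-DBS switch-on", and the food reward task (LOFPQ) follows each MEG scan.
- **The clinical battery.** Phase II and Phase IV have it repeated monthly. With switch-on only at the end of month 3, this implies a clinical assessment before switch-on.
- **Weekly True Colours ratings.** These run from study entry to study end.

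The Data Analysis section gives none of these the role of reference.

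**The concern.** The study has no parallel control group, so what a within-patient difference means depends on where it starts. A difference that starts at month 1 spans anaesthesia, bilateral electrode insertion, an inpatient stay, a brief test activation the day after surgery, and the weeks before therapeutic stimulation begins. Any lasting change from these events, or from time and expectancy, enters the difference at every later visit.

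The introduction describes DBS as the delivery of electrical pulses, and Phase IV presents the assessments as tracking change that results from DBS. If the month-1 difference is reported as an established treatment effect, readers will take it as the effect of stimulation. That bears on the study's second aim, to map neural mechanisms and symptomatic change following DBS.

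**Working it through.** The documents state no power, alpha, effect size or standard deviation, so there is no figure to reproduce. The check has two parts: the timeline, and an illustration on assumed inputs.

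**1. What each comparison spans**

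| Comparison | Starts | Ends | Surgery inside the interval? | Blinded? |
|---|---|---|---|---|
| Month-1 baseline vs a visit after switch-on | Before surgery | Up to month 15 | Yes | No |
| Pre-switch-on vs a visit after switch-on | After surgery, by end of month 3 | Up to month 15 | No | No |
| On vs off | Month 10 | Month 10 | No | Yes |

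The first row includes the operation and about two months without therapeutic stimulation. The blinded row covers 2 × 2 = 4 weeks. The follow-up after switch-on lasts about 12 months, and apart from those 4 weeks it is informed only by the open-label rows.

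**2. How far a non-stimulation shift could mislead (assumptions, not document figures)**

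Suppose stimulation has no effect, but scores shift by s baseline SDs between month 1 and follow-up for other reasons. Let r be the correlation between the two measurements.

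- SD of change = √(2(1 − r)), in baseline SDs.
- Standardised shift = s / √(2(1 − r)).
- Probability of p < 0.05 = rejection probability of a two-sided paired t-test, n = 6, from the noncentral t distribution with noncentrality √6 × standardised shift.

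| s | r = 0.5 (SD of change 1.000) | r = 0.7 (0.775) | r = 0.9 (0.447) |
|---|---|---|---|
| 0.10 | 5.5% | 5.8% | 7.4% |
| 0.25 | 8.0% | 10.0% | 20.1% |
| 0.50 | 17.1% | 25.2% | 59.6% |

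If the whole shift happens before switch-on and persists, a pre-switch-on reference returns the error to 5%.

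**3. Regression to the mean alone (also assumed)**

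If selected patients score z SDs beyond a population mean, the expected return is (1 − r) × z.

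- z = 0.25, r = 0.9: 0.1 × 0.25 = 0.025 SD; 0.025 / 0.447 = 0.06; rejection about 5%.
- z = 0.5, r = 0.6: 0.4 × 0.5 = 0.20 SD; 0.20 / 0.894 = 0.22; rejection 7.4%.
- z = 1.5, r = 0.6: 0.4 × 1.5 = 0.60 SD; 0.60 / 0.894 = 0.67; rejection 26.8%.

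The range starts at the nominal level, and its upper end needs an extreme combination. The documents give neither z nor r.

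**4. What the blinded contrast can carry**

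With the same test, 80% power needs a standardised within-patient difference of about 1.43 at n = 6, or 1.68 at n = 5. The on/off contrast is free of the surgical confounding but can detect only large differences.

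**The case against.** The strongest reply is that the plan also contains a sound comparison. The on/off contrast is within patient, double-blind and months after surgery. Neither surgery nor regression from baseline can pass for stimulation in it. This stands. A reader might infer from the opening of the Data Analysis sentence that all treatment effects rest on the pre-operative baseline; the rest of the sentence shows that only one of two comparisons does.

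Other stronger readings are also tempting and not supported:

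- **That everything between month 1 and switch-on is credited to stimulation.** The article speaks of treatment effects, and total change from pre-operative status is a legitimate quantity for an implanted device. A monthly visit before switch-on would itself be one of the planned comparisons, so the early change would be visible. What is missing is its use as a reference.
- **That MEG change will be judged against the scan taken without implanted hardware.** The article names no MEG reference scan, and it schedules several scans with hardware in place.
- **That the habit task and CANTAB are absent at month 3.** Phase IV says they "will be carried out twice during the DBS on-off phase and at the end of the study", but refers to Figure 1 for the schedule, and that figure is not shown. Five of at most six patients are already enrolled.
- **That regression to the mean is large.** Ranking candidates by severity and distress favours it. Illness of more than seven years, and the exclusion of unstable physical states and current severe depression, limit it. Ranking also precedes the baseline measurement, so some regression may already have happened by then.

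Finally, a pre-switch-on reference is imperfect. It follows a brief test activation. Residual post-surgical discomfort would worsen the reference and flatter later scores, although the protocol has such effects settle before switch-on. It does not remove expectancy or time trends after switch-on. These limits stand, and they are the reason to show both references.

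**Conclusion.** The point holds for the comparison of baseline with monthly follow-up. As a measure of stimulation it is confounded with implantation, peri-operative care and time, and a closer reference is already scheduled: explicitly for MEG and the LOFPQ, by implication for the clinical battery, and through the weekly ratings for True Colours. The blinded on/off contrast is unaffected, but it does not cover the open-label course to month 15.

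The size cannot be determined from the documents. The illustration runs from close to 5% for small shifts to well above it for a shift of half an SD, and rests wholly on assumed shifts and correlations. Given an explicitly exploratory study of up to six patients with a sound second comparison, this is a correction worth making before analysis, not a flaw that invalidates the plan.

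**What to change.** In the Data Analysis section:

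1. For open-label change after switch-on, name the post-operative, pre-switch-on assessment as the reference for stimulation-related change: the month-3 MEG scan and LOFPQ, the last monthly battery before switch-on, and the True Colours ratings from the weeks just before switch-on.
2. Keep the month-1 baseline for the total change from implantation plus stimulation, and label it so.
3. Report the change from month 1 to pre-switch-on separately.
4. Rest causal statements on the blinded on/off contrast, and describe open-label changes as estimated, not established.
5. For MEG, base stimulation contrasts on scans with the hardware implanted: month 3, month 10 on and off, and month 15.

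The cost is analysis wording and some extra rows in the results tables; no visit or test is added. Show both references side by side, with a note that the pre-switch-on score may carry some surgical discomfort, follows a brief test activation, and leaves later expectancy and time trends in place.

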### Data Monitoring

Data monitoring for the project will be conducted by the CI and co-investigators. The study may also be audited by the CTRG. There will be no external monitoring of the study. The project will be under ongoing review for safety and efficacy by the CI and [name]. The study may also be audited by the CTRG, with extensive protocols from the University of Oxford. Any SAE directly relating to the DBS electrode insertion and which cannot be immediately resolved will result in electively stopping the trial prematurely.

## Participant Confidentiality

The study team will ensure that the participants’ anonymity is maintained. A basic dataset of name, age, predominant symptoms and medications will be recorded. All electronic data will be anonymised with the date of recording and a unique project number as the only identifiers. It will be stored on secured university servers and is covered by the Oxford University Data protection register (reference No. Z575783X). All non-anonymised paper data (e.g., consent forms) will be stored in a locked cupboard within a secure building. All paper records will be kept in the research department at all times.

### Capacity and Informed Consent

Ethical issues are of major importance in the treatment of AN and will be the focus of an ethical sub-study (detailed in section Phase V: Ethics Sub-Study) (52). Only patients with full capacity, fully consenting and voluntarily entering into the study will be eligible.

### Burdens

The study does involve a number of return visits for outpatient assessment and follow-up, and includes up to 4 days spent in hospital for the DBS surgery in order for these assessments to be carried out. Therefore, we will aim to recruit patients who are physically mobile and are prepared and able to return for multiple assessments as outlined. However, involvement is entirely voluntary, and the patient can withdraw at any time.

## Discussion

We have presented an innovative clinical trial protocol, applying DBS research to individuals with SE-AN. We hope this will guide future researcher, ethics committees and the development of technologies designed for psychiatric populations. We recommend this protocol as a starting point to guide future trials. We further suggest that the neuroethical framework we have now published (52) should also be incorporated in such experimental treatment trials in SE-AN, due to unique concerns regarding physical wellness and capacity. The protocol we describe incorporates this ethical gold standard (52), which acts in synergy with the main trials protocol described here. It serves as means to investigate, empirically, the ethics of such an experimental treatment. Incorporating neuroethical standards centrally within novel neurotechnology research aims to ensure that rigorous and continuous ethical input is available. This is of great importance given the sensitive and challenging nature of this research, and it is essential that the welfare of vulnerable participants is maximally protected. Our protocol exemplifies the Nuffield Council of Bioethics’ recommendations regarding the ethics of novel neurotechnology (2013) (79). We believe that the clinical trial described here can contribute to treatment development for AN and the ethics of such research in addition to extending the boundaries of DBS science.

## Availability of Data and Materials

The authors can confirm that all relevant data are included in the article. Data generated by the protocol will be included in subsequent publications and/or supplementary information files once the study is completed. Dissemination will be by presentation at conferences and in peer-reviewed publications.

## Insurance

In the event of any participant suffering harm as a result of their involvement in the research, the University has a specialist insurance policy in place which would operate (Newline Underwriting Management Ltd., at Lloyd’s of London, policy numbered: WD1200463).

## Trial Status

The trial status is ongoing, and recruitment commenced on 8 October, 2013. Active recruitment had to be paused after the first patient due to MEG scanner refurbishment (4/15–4/16): protocol version 6, dated 11 November, 2016. To date, five participants have been enrolled in the study. The study has been approved by NRES Committee South Central—Oxford A REC (Ref: 13/SC/0267) and is registered at clinicaltrials.gov (NCT01924598).

## Ethics Statement

Ethics approval and consent: this study will be carried out in accordance with the recommendations of NRES: South Central—Oxford A Research Ethics Committee (REC) Ref: 13/SC/0267. Informed written consent will be taken care by RP, in accordance with the Declaration of Helsinki. Consent can be freely withdrawn at any point with no effect on their usual clinical care.
